### Outcome measures

Primary outcomes include feasibility, acceptability, and safety of the protocol. To assess feasibility the: 1) time taken to complete the recruitment of all participants, 2) proportion of participants recruited from the total number screened, and 3) blinding success will be collected using a blinding questionnaire where participants will be asked to indicate which study group they believe they were assigned to and rate their confidence in their choice. To measure the acceptability of the protocol: 1) protocol adherence rate (target ≥ 80%), 2) number of dropouts in each of the treatment and sham groups (target ≤ 20%), and 3) the willingness of participants to undergo therapy (in the form of an 11-point scale (0–10) completed during the baseline assessment session, target: at least 7/10 in ≥80% of participants), will be collected. This questionnaire was included based on prior evidence that individuals with SCI are generally interested in participating in physiotherapy based clinical trials but may be less certain when interventions involve electrical stimulation [41]. Safety will be monitored throughout the trial using a standardized adverse event case report form. At each session, participants will be asked about any new or ongoing adverse events, and any event identified will be documented with its onset date, resolution date, detailed description, and severity, classified according to the Common Terminology Criteria for Adverse Events (CTCAE) [42]. Events will also be categorized as serious or non-serious, expected or unexpected, and their relationship to the study procedures will be recorded. For serious adverse events, information on the nature of the event (e.g., hospitalization, life-threatening occurrence, disability) will be captured. The outcome of each event and its impact on study participation will also be documented. All safety data will be reviewed descriptively to inform the feasibility and safety profile of the protocol for a future definitive trial.

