### Data analysis and management

This is a pilot study designed to inform the development of a protocol for a definitive randomized controlled trial. As this is a pilot trial, the sample size was not determined through a formal power calculation. Instead, the target of 14 participants (7 per group) reflects pragmatic considerations related to recruitment feasibility in individuals with iSCI, a population with known challenges in enrollment [49,50]. Methodological guidance indicates that feasibility focused pilot studies may appropriately include smaller sample sizes when the primary objectives are to assess recruitment, adherence, safety, and protocol procedures rather than to obtain precise estimates of treatment effects [30,51,52]. Pilot trials in SCI population frequently use similarly small samples due to the clinical characteristics and limited pool of eligible participants [49]. Outcomes related to demographics, feasibility, acceptability, and safety will be reported descriptively [53]. For the secondary outcomes, mean scores and mean changes over time will be summarized descriptively to explore preliminary trends in the effectiveness of the intervention. Reasons for any missing values will be categorized and reported, allowing for patterns to be analyzed to evaluate the acceptability of the intervention and the burden of the protocol. Consistent with the exploratory nature of this study, analyses will be interpreted descriptively rather than through formal hypothesis testing, with emphasis placed on patterns of change across time and between groups. Because the study includes repeated measurements, results will be organized by timepoint to reflect within group changes over the study period, and between group differences will be described accordingly. Effect sizes with confidence intervals will be calculated for each group using Cohen’s d to provide estimate of the magnitude of change and to support planning a future definitive trial [30,54]. Given the pilot nature and small sample size, effect sizes will be interpreted cautiously, recognizing their potential instability and risk of overestimation. Lastly, data will be used to inform the sample size calculation for the definitive randomized controlled trial based on the minimum clinically important difference (MCID) in walking speed [55]. In iSCI, the MCID for walking speed is 0.13m/s [56]; power will be set at 80%, alpha at 0.05 and a dropout rate based on the findings of the pilot trial. As this is a single site pilot trial a data safety and monitoring committee (DSMC) is not required.

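### Per-group Cohen's d with 7 people per arm overstates the standardised change by about 8% to 15% on average; the plan names neither the standardiser nor a small-sample correction (minor)

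*Protocol article*

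**What the plan says.** The relevant text is in the protocol article under Data analysis and management.

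- **Estimator:** "Effect sizes with confidence intervals will be calculated for each group using Cohen’s d to provide estimate of the magnitude of change". The stated purpose is "to support planning a future definitive trial". The text does not say which SD is the divisor and mentions no small-sample correction.
- **Size:** "the target of 14 participants (7 per group) reflects pragmatic considerations".
- **Caveat:** the following sentence says that "effect sizes will be interpreted cautiously, recognizing their potential instability and risk of overestimation".
- **Sample size of the definitive trial:** this takes another route: "the MCID for walking speed is 0.13m/s [56]; power will be set at 80%, alpha at 0.05", with dropout taken from the pilot.

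The same section also plans raw mean scores and mean changes over time, and it rules out formal hypothesis testing.

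**The concern.** Cohen's d divides a mean change by a sample SD. In small samples the reciprocal of the sample SD is too large on average, so d is biased away from zero. The bias is a multiplicative factor set by the degrees of freedom of the SD, and it is at its most noticeable with samples as small as these.

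The plan treats overestimation as something to bear in mind when reading the results. That is the only possible answer to noise, but this part of the overestimation can be calculated and divided out.

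Two things are at stake. First, d is the only standardised magnitude the article names for strength, walking, sit-to-stand, timed-up-and-go and sway, and later readers may take the published values at face value. Second, the factor depends on how many people are analysed, so unequal dropout gives the two arms different inflation in a report that sets their patterns of change side by side.

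**Working it through.** The article states no effect size or power figure, and its 14 participants are a pragmatic target, so there is no figure of the plan's own to reproduce. The check is on the size of the bias.

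**Inputs.** From the article: 7 per arm; Cohen's d per group; difference of 0.13 m/s, 80% power, alpha 0.05. Assumed: normal data; no correction applied; pre/post correlation 0.5 to 0.9 where it matters; two-sided alpha; SD of walking speed 0.15 to 0.40 m/s, for illustration only.

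**1. SD of change or baseline SD of one arm (m = n − 1 degrees of freedom).** The mean of d is δ / J(m), where δ is the true standardised change and J(m) = Γ(m/2) / [√(m/2) · Γ((m−1)/2)].

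| Number analysed | m | J(m) | 1/J(m) | Mean inflation |
|---|---|---|---|---|
| 7 | 6 | 2 / (1.732 × 1.329) = 0.869 | 1.151 | 15.1% |
| 6 | 5 | 0.841 | 1.189 | 18.9% |
| 5 | 4 | 0.798 | 1.253 | 25.3% |

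Simulation with 500,000 replicates at n = 7 gave ratios of 1.149 to 1.152 for these two standardisers, which agrees with the formula.

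**2. Pooled pre/post SD.** The same simulation at n = 7 gave ratios of 1.084, 1.112 and 1.127 for correlations of 0.5, 0.8 and 0.9, that is, about 8% to 13%.

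**3. Unequal arms.** With the same true change and 7 against 6 people analysed, the mean values of d differ by 1.189 / 1.151 = 1.033, about 3%.

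**4. Between-group d.** With 7 + 7 people and a pooled SD, m = 12, J = 0.936 and 1/J = 1.068, an inflation of 6.8%.

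**5. Bias against noise.** Take a true d of 0.5 at n = 7, standardised by the SD of change. From the noncentral t distribution, d has mean 0.576, SD 0.508 and a 95% range of −0.27 to 1.73. The bias is 0.576 − 0.5 = 0.076, and 0.076 / 0.508 = 0.15, about one seventh of the sampling SD.

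**6. Does d enter the planned sample size?** The planned route is n per arm = 2 (1.960 + 0.842)² × (SD / 0.13)². This gives 21 per arm for an SD of 0.15 m/s, 59 for 0.25 and 149 for 0.40, before dropout. The pilot can inform the SD and the dropout rate; d appears nowhere.

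**The case against.** The case against is substantial, and most of it limits the point rather than removing it.

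- **That no correction will be applied is inferred.** The article excludes none, and a fuller analysis plan may specify one. This stands as a condition. However, the article does name its estimator, and the usual reading of that name is the plain form.
- **The amount is not a single number.** With the standardiser unstated, the range at n = 7 is about 8% to 15%. This stands, and it is why the standardiser should be named.
- **The plan already warns of overestimation and calls its findings exploratory.** True, but a warning does not remove a known factor.
- **Imprecision dominates.** This stands: correction leaves the estimates nearly as uninformative as before.
- **The factor is exact only under normality.** This also stands. WISCI II and LEMS are bounded scores and the timed tests may be skewed, so for those outcomes the correction is approximate.

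A reader might go on to three stronger conclusions that the article does not support.

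- **That the definitive trial will be too small.** If an inflated d from 7 people were used directly, the size would shrink by the factor 0.869² = 0.755, for example from 63 to 48 per arm at a true d of 0.5. The article proposes no such calculation. Its route uses the 0.13 m/s difference, and a within-group d would in any case be the wrong contrast for a two-arm trial.
- **That inflation of 25% is to be expected.** This needs an arm of 5. Losing 2 of 7 is 29%, beyond the article's own 20% dropout target if that is read per arm. Losing 1 of 7 is 14%, and the figure is then 19%.
- **That every reported d will look too favourable.** The factor is an average, so single estimates can fall below the truth. It also pushes away from zero in either direction, so it flatters the intervention only where the true change is an improvement.

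**Conclusion.** The point holds as a minor one. If Cohen's d is computed in its plain form, per-group values will on average overstate the size of the standardised change by 15% at n = 7 and 19% at n = 6 with the SD of change or baseline SD, or by about 8% to 13% at n = 7 with a pooled pre/post SD and a correlation of 0.5 to 0.9. This rests on normality and on no correction being applied.

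No stated decision of the trial depends on it: the planned sample size is unaffected, and sampling error is about seven times the bias at a true d of 0.5. It is worth correcting because the bias is systematic and computable, and because at present it would differ between arms that lose different numbers of people.

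**What to change.** In Data analysis and management:

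1. Name the standardiser: SD of change, baseline SD, or pooled pre/post SD.
2. Replace Cohen's d with the bias-corrected form, Hedges' g = J(df) × d, taking J from the degrees of freedom of the SD actually used and the number actually analysed. With the SD of change or baseline SD, J = 0.869 for 7 people and 0.841 for 6.
3. Use a confidence interval suited to that standardiser. The noncentral t distribution serves if the SD of change is used; the other choices need their own interval.
4. Apply the same correction to any between-group d (J = 0.936 at 12 degrees of freedom).

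Raw mean changes are already planned and need no addition; they should stand beside the standardised values.

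The cost is a sentence or two of analysis wording and one multiplier in the code, with no new data and no change to trial conduct. The only downside is that reported effect sizes become up to about 13% smaller at n = 7 (1 − 0.869 = 0.131).

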**Methods:**

This is a pilot randomized controlled trial with assessor and participant blinding. Fourteen participants will be randomized to receive either active or sham rTMS prior to FES cycling for a total of 12 sessions over six weeks. Functional outcomes, including gait parameters, muscle strength, and balance tests, will be assessed at baseline, midpoint, post-intervention, and two weeks following treatment cessation and will be assessed both within and between groups to explore trends in efficacy. Feasibility and safety data will be analyzed descriptively.

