The primary objectives of this study are to: 1) evaluate the feasibility, acceptability, and safety of a protocol combining rTMS with FES cycling in individuals with iSCI, and 2) provide data for a sample size calculation to inform a full randomized controlled trial. The secondary objective is to explore the effects of combining rTMS with FES cycling on lower extremity function including muscle strength, walking function, and postural sway in quiet standing, to identify trends and inform sample size estimation for future definitive trials. Since the goal of this pilot is to test the feasibility of adding rTMS to an established rehabilitation modality, the design of this trial does not include an rTMS-only arm. This approach is supported by the broader SCI literature, which consistently describes rTMS as most effective when paired with active motor training rather than applied in isolation. Recent reviews note that rTMS is commonly delivered alongside task specific rehabilitation to enhance corticospinal excitability and functional recovery [25,26]. Therefore, all participants will receive FES cycling, and the comparison focuses on real versus sham rTMS to explore early signals of additive benefits.

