### Randomization and blinding

Participants will be randomized to either the active rTMS intervention group or the sham rTMS control group using a 1:1 allocation ratio; all participants will receive active FES cycling. Randomization will be blocked by four and stratified by the American Spinal Injury Association Impairment Score (AIS) of C or D. An individual who is not a member of the research team will perform draws for the group assignment. Participant blinding in this protocol will be achieved using a sham rTMS coil, which functions through distribution of the electrical field so there is no focal stimulation over the cortex. As a result, the magnetic field generated is insufficient to induce an electrical response in the underlying tissue. The sham coil is identical in shape, color, and weight to the active coil and produces the same auditory and somatosensory sensations on the scalp associated with active stimulation. The study assessor will also be blinded to group assignment until data analyses are complete. Only the rTMS technician will be aware of group allocation; unblinding will be allowed if an adverse or unexpected event occurs.

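### Effect sizes with confidence intervals are specified only for change within each arm; the real-versus-sham difference is to be described, but with no stated effect size or interval

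*Protocol article*

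**What the plan says.** The secondary, functional outcomes are handled under Data analysis and management in the protocol article. Means and mean changes are summarised by timepoint without formal hypothesis testing, "with emphasis placed on patterns of change across time and between groups". For the comparison of arms the text says that "between group differences will be described accordingly" and names no statistic.

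The only effect size and the only confidence interval specified come next: "Effect sizes with confidence intervals will be calculated for each group" by Cohen's d, "to provide estimate of the magnitude of change and to support planning a future definitive trial". Read plainly, this is a standardised change over time, computed separately in each arm. The section adds that effect sizes will be read with caution because of small numbers. It then bases the definitive trial's sample size on an MCID of 0.13 m/s in walking speed, 80% power, alpha 0.05 and the pilot's dropout rate.

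Three other places bear on the point. The Introduction says that "the comparison focuses on real versus sham rTMS to explore early signals of additive benefits". The Randomization and blinding section says that "all participants will receive active FES cycling". The abstract's Methods paragraph says that outcomes "will be assessed both within and between groups to explore trends in efficacy".

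**The concern.** Randomisation protects one quantity here: the difference between active and sham rTMS, given that everyone cycles with FES. Change within an arm is not protected. In the active arm it is the sum of FES cycling, the passage of time, repeated testing, outside therapy (which the Discussion says is not formally tracked) and any rTMS effect. In the sham arm it is the same sum without rTMS.

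The plan puts its only stated measure of uncertainty on these two sums and none on their difference. A results table built to this wording would show an interval for each arm and no interval for the contrast. The natural but invalid step is then to note that one interval clears zero and the other does not, and to credit rTMS. With no hypothesis tests planned, the intervals carry most of the inferential weight, so it matters which quantity they describe.

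The same sentence gives the per-arm values a role in planning the definitive trial. An MCID-based calculation has no use for a within-arm d.

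**Working it through.** **Plan's own figure.** The sample size is stated as pragmatic: 7 per group, 2 × 7 = 14, which agrees. There is no power or precision figure to reproduce.

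**Step 1: what each quantity contains.**
- Active-arm change = FES + time + practice + other therapy + rTMS.
- Sham-arm change = FES + time + practice + other therapy.
- Active minus sham = rTMS, in expectation, because of randomisation.

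Only the third line answers the question in the Introduction. Only the first two are given an effect size and interval.

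**Step 2: how often the two per-arm intervals would mislead.** From the document: n = 7 per arm. Assumed: zero rTMS effect, normal changes, independent arms, and the same true standardised change d in both arms (mean change divided by the SD of change). The document gives no value for d, so a range is shown.

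The 95% interval for one arm's mean change lies above zero when its t statistic exceeds the 97.5% point of t on 6 df. That statistic is noncentral t on 6 df with noncentrality d√7. Call the probability p. The pattern of active above zero and sham not has probability p(1 − p).

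| Assumed d | p | p(1 − p) |
|---|---|---|
| 0.3 | 0.099 | 0.089 |
| 0.5 | 0.200 | 0.160 |
| 0.8 | 0.428 | 0.245 |
| 1.0 | 0.600 | 0.240 |

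So the pattern arises in about 9% to 24% of trials in which rTMS does nothing. Because p(1 − p) peaks at 0.25, it cannot exceed 25% under these assumptions. At d = 1.2 it has fallen to 0.186. A between-arm 95% interval on the same data would lie wholly on the side favouring rTMS in 2.5% of such trials, whatever the value of d.

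**Step 3: precision of the contrast.** The exact interval inverts the noncentral t on 12 df, with observed t = d√(7/2).
- Observed d = 0: −1.05 to 1.05.
- Observed d = 0.5: −0.58 to 1.56.
- Observed d = 0.8: −0.31 to 1.88.

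**Step 4: what the MCID calculation needs.** By the normal approximation, n per arm = 2(1.96 + 0.84)² × (SD/0.13)², taking alpha as two-sided (the document does not state sidedness). For assumed gait-speed SDs of 0.10, 0.15, 0.20, 0.25 and 0.30 m/s this gives 10, 21, 38, 59 and 84 per arm, or 20, 42, 76, 118 and 168 in total before dropout. The result depends on the SD and then on dropout. A within-arm d does not enter.

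**The case against.** A reader might infer that the trial never estimates real versus sham. The text does not support that. The analysis section and the abstract both plan a between-group description, and a described difference in mean change is a point estimate of the contrast. What is missing is a stated effect size and interval for it.

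A reader might also take 9% to 24% as the plan's error rate. It is not. The plan declares no rule that compares each interval with zero, and it rules out formal testing. The Discussion calls all findings exploratory, and the sham arm's d and the between-group description would stand beside the active arm's d. The percentages size a misreading that the layout invites, and they rest on an assumed d. This part of the objection stands.

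Nor is the definitive trial's size shown to be at risk. It rests on the 0.13 m/s MCID, and effect sizes can inform planning without setting the target difference. The planning phrase needs clarifying, but no miscalculation follows from it.

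Finally, caution about effect sizes is already promised. That caution concerns instability and overestimation in a small sample, so it covers the upward bias of Cohen's d and makes a small-sample correction optional. It does not cover the mixing of FES and rTMS effects within an arm, which no sample size removes.

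**Conclusion.** The point holds in this form: the plan specifies effect sizes and intervals for the wrong quantity and leaves the randomised contrast with a description only. This is a stated choice of method that does not fit the design, not a detail left to a fuller document. The conclusion follows from the wording and from FES cycling being given in both arms, and needs no numerical assumption. Only the illustration (9% to 24% against 2.5%) depends on an assumed common within-arm d of 0.3 to 1.0, normality, and no rTMS effect.

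Severity is moderate. The outcomes affected are secondary and exploratory in a feasibility pilot, no primary outcome or safety conclusion depends on the sentence, and the data for the contrast will be collected anyway.

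**What to change.** Replace the effect-size sentence with wording to this effect:

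- For each continuous secondary outcome, report the active-minus-sham difference in change from baseline at weeks 3, 6 and 8, in natural units (m/s for gait speed), with a 95% confidence interval, preferably adjusted for the baseline value. Hedges' g with its interval may be added as an optional standardised version.
- Show within-group changes descriptively only, and do not use them as evidence of an rTMS effect.
- State that the pilot supplies the SD and the dropout rate to the MCID-based sample size, and that no observed d will be used for it.

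The ordinal, bounded scales (WISCI II, LEMS) can stay as descriptive summaries by arm. The Global Rating of Change has no baseline value, so it too is simply summarised by arm.

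The cost is a change of wording, with no new data, visits or participants. It is best settled before unblinded analysis. The downside is that the interval will look wide: about −0.58 to 1.56 in standardised units for an observed d of 0.5. That is the precision 7 per arm can give, and reporting it is better than leaving it unstated.

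### The only stated confidence intervals are on a unitless within-arm Cohen's d; none is stated in m/s or on the active-minus-sham difference (low severity)

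*Protocol article*

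**What the plan says.** All of the analysis wording is in the protocol article, section Data analysis and management.

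- **Raw-unit summaries:** for the secondary outcomes, "mean scores and mean changes over time will be summarized descriptively". No interval is named.
- **Between arms:** results are organised by timepoint, and "between group differences will be described accordingly". No estimator or interval is named.
- **Intervals:** "Effect sizes with confidence intervals will be calculated for each group using" Cohen's d, as a measure of how large the change is, and also "to support planning a future definitive trial". This is the only mention of confidence intervals in the article. The standardising SD is not given.
- **Future trial:** its size is to rest on walking speed, where "In iSCI, the MCID for walking speed is 0.13m/s", and "power will be set at 80%, alpha at 0.05 and a dropout rate based on the findings of the pilot trial".
- **Pilot size:** "the target of 14 participants (7 per group) reflects pragmatic considerations". No SD of walking speed is quoted.

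The end of the Introduction says that every participant receives FES cycling and that the comparison of interest is real against sham rTMS. The analysis section excludes formal hypothesis testing and warns that effect sizes may be unstable and too large.

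**The concern.** The stated measure of uncertainty does not match either quantity that the pilot is meant to inform.

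1. **Contrast.** The question is what active rTMS adds to FES cycling. A d for each arm describes before-after change within that arm. It includes the effect of FES cycling, practice and any outside therapy, so an interval around it says nothing directly about active against sham.
2. **Scale.** The planning quantity is a difference in m/s. An interval on d cannot be set beside 0.13 m/s unless the SD is known and the interval is converted.
3. **Denominator.** If each arm is divided by its own SD, the two d values are on scales that differ by chance. Readers will nevertheless compare them side by side.

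At stake is how readable the pilot's functional results are: whether a reader can see how little 14 people say about a gain of 0.13 m/s. The primary feasibility, acceptability and safety outcomes are not affected.

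**Working it through.** The plan contains no calculated figure to reproduce: the 14 is pragmatic and no SD is given. Every SD below is therefore an assumption.

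**Inputs.** From Data analysis and management: n = 7 per arm, 0.13 m/s, 80% power, alpha 0.05 (taken as two-sided). Assumed: SD of change in walking speed 0.10 to 0.30 m/s.

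**1. One gain, several values of d.** With d = gain / SD and a noncentral-t 95% interval at n = 7, a gain of 0.13 m/s gives:

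| Assumed SD of change (m/s) | d | 95% CI |
|---|---|---|
| 0.10 | 0.13/0.10 = 1.30 | 0.24 to 2.31 |
| 0.20 | 0.13/0.20 = 0.65 | −0.19 to 1.45 |
| 0.30 | 0.13/0.30 = 0.43 | −0.36 to 1.20 |

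The d value alone does not show whether 0.13 m/s was reached.

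**2. Chance difference between two arm SDs, if each arm uses its own.** With equal true SDs, the ratio of sample variances follows F(6,6).
- Ratio of SDs at least 1.5: 2 × P(F ≥ 1.5²) = 0.347.
- Ratio of SDs at least 2: 2 × P(F ≥ 2²) = 0.116.
- With 6 per arm, F(5,5): ratio at least 1.5 has probability 0.394.

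**3. How much this adds to the gap between the arms' d values.** I simulated two arms of 7 with the same true gain (0.13 m/s) and the same true SD of change, 400,000 runs, and took the absolute difference between the two d values.

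| Assumed SD (m/s) | Median gap, separate SDs | Median gap, pooled SD | Share remaining |
|---|---|---|---|
| 0.15 | 0.48 | 0.37 | 78% |
| 0.20 | 0.45 | 0.37 | 83% |
| 0.30 | 0.42 | 0.37 | 87% |

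At SD 0.20 the 90th percentile falls from 1.20 to 0.95, and the variance of the gap falls by about 40%. Separate SDs thus lengthen the tails, but the typical gap is mainly noise in two means of seven people, which no choice of standardiser removes.

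**4. What the interval in original units would look like.** Half-width of the between-arm 95% interval = t(0.975, 12) × SD × √(2/7) = 2.179 × 0.5345 × SD = 1.165 × SD.

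| Assumed SD (m/s) | Half-width (m/s) | n per arm of a trial to detect 0.13 m/s, before dropout |
|---|---|---|
| 0.10 | ±0.116 | 10 |
| 0.15 | ±0.175 | 21 |
| 0.20 | ±0.233 | 38 |
| 0.25 | ±0.291 | 59 |
| 0.30 | ±0.349 | 84 |

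The half-width exceeds 0.13 m/s once the SD exceeds 0.13/1.165 = 0.112 m/s. The last column shows that what the future sample size needs from this outcome is its SD in m/s. A d does not supply that by itself.

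**The case against.** The case against is substantial, and much of it stands.

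- **The standardiser is not stated.** A d for each group over one SD pooled across all 14 people also fits the wording. A reader might infer that the plan divides each arm by an SD from seven people. That is a natural reading but not a stated fact, and the choice could properly sit in an analysis plan that is not shown. The 35% figure applies only under that reading.
- **SD noise is not the main source of the gap.** A reader might infer that a difference between the arms' d values would mostly reflect the two SDs. The simulation does not support this: about 80% of the typical gap remains with a pooled SD.
- **Values in m/s are not lost.** Mean changes will be reported, so point values can be set beside 0.13 m/s. If d uses the SD of change, mean change and d together return that SD, and with n an interval can be rebuilt.
- **The definitive trial does not rest on d.** Its target difference is the MCID, so an unstable d would not set it.
- **Caution is already written in.** The article warns about unstable effect sizes, plans no tests, and calls the findings exploratory in the Discussion.
- **The replacement interval will be wide.** For most plausible SDs it could rarely separate zero from 0.13 m/s.

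What these points do not answer is the mismatch itself. The article positively chooses where intervals go, and it puts them on a unitless within-arm quantity while naming a between-arm question and a benchmark in m/s. General caution about effect sizes does not supply the interval on the relevant scale. A wide interval is also the honest description of 14 participants, not a reason to leave it out.

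**Conclusion.** The point holds in a limited form. The stated confidence intervals are on Cohen's d within each arm, and none is stated in m/s or on the active-minus-sham difference, although those are the scale and the contrast that the plan itself names. Separate arm SDs, if used, would add avoidable noise (a ratio of 1.5 or more in about 35% of pilots), but only as a secondary contribution: the median gap is 0.45 against 0.37 at an assumed SD of 0.20 m/s.

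These figures assume normal changes, equal true SDs, seven completers per arm and d standardised by the SD of change. The 35% does not depend on the SD value. The gap and half-width figures do.

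Severity is low, a change to consider. Function is a secondary outcome, mean changes in m/s will be available, and the future sample size rests on the MCID.

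**What to change.** In Data analysis and management, replace the per-group d as the main estimate. Suggested wording: *For each functional outcome and timepoint we will report the mean change from baseline in each arm and the active-minus-sham difference in mean change, in original units, each with a t-based 95% confidence interval. Walking speed will be shown beside 0.13 m/s for description, without a test. If Cohen's d is also given, both arms will be divided by the same SD pooled across arms, and that SD will be named.*

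State beforehand that the between-arm interval will be wide (about ±1.16 × SD, for example ±0.23 m/s at an assumed SD of 0.20) and that it is reported to show the uncertainty, not to judge efficacy.

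The cost is a few sentences and slightly more reporting, with no new data and no burden on participants. The one drawback is that the imprecision becomes visible, which suits a pilot that already describes its findings as exploratory.
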